### Recruitment {15}

The iDoT-AFD study enrolls 480 patients with AFD (120 per treatment group), 100 patients with BD, and 100 healthy participants.

### Assignment of interventions: allocation

#### Sequence generation {16a}

For each center, a randomization list has been made using software-generated randomized numbers by a research assistant without clinical participation in the trial. Randomization is stratified for each clinical site. A block randomization is conducted in an allocation ratio of 1:1:1:1 with a fixed block length per center.

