## Methods: participants, interventions, and outcomes

### Study setting {9}

This clinical trial is sponsored by Shanghai Mental Health Centre (SMHC), [name]. Five clinical sites are involved to recruit participants (SMHC, Wuhan Mental Health Center, the Affiliated Brain Hospital of Guangzhou Medical University, Dalian Seventh People’s Hospital, and Xijing Hospital of the Fourth Military Medical University), each with a principal investigator (PI) and a clinical trial coordinator (CTC). The iDoT-AFD study also includes biomedical engineering experts from Shanghai Jiao Tong University and ShanghaiTech University to ensure high-level data mining.

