#### Strategies to improve adherence to interventions {11c}

Every participant has a fixed investigator for assessments at baseline and follow-up, and the investigator will keep in touch with the participant to provide encouragement and remind the patients of taking medicine.

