#### Concealment mechanism {16b}

The randomization codes are packed into sealed envelopes in sequence. The envelopes are locked in a cabinet by a research nurse per center, and each envelope will be opened in ascending order to assign intervention after a patient with AFD is recruited.

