#### Implementation {16c}

The research assistant without clinical participation in the trial will generate the allocation sequence. Trained investigators will enroll participants. The research nurse at each center will keep and open the envelopes containing randomization codes.

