### Assignment of interventions: blinding

#### Who will be blinded {17a}

The iDoT-AFD is an open-label study without blinding.

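### The examiner-rated primary outcome is scored by each participant's own unblinded investigator; secondarily, a fixed block length per centre makes some allocations deducible

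*Protocol article*

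**What the plan says.** All references are to the protocol article.

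**Outcome and rater.** Outcomes {12} makes examiner-rated remission the primary outcome: a HAMD-24 total of 7 or less at the end of week 12. To the question of who is blinded, section {17a} answers: "The iDoT-AFD is an open-label study without blinding". Section {11c} states: "Every participant has a fixed investigator for assessments at baseline and follow-up". It gives that same investigator the tasks of keeping in touch, encouraging the patient and reminding them about medication. Section {18a} makes the week-12 visit face-to-face, with clinical assessments also at weeks 2, 4 and 8. Statistical methods {20a} plans a repeated-measures mixed model on HAMD totals.

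**Allocation.** Each centre has its own list. Section {16a} states: "Randomization is stratified for each clinical site", and then: "A block randomization is conducted in an allocation ratio of 1:1:1:1 with a fixed block length per center". The length itself is not given. On concealment, {16b} states: "The randomization codes are packed into sealed envelopes in sequence". A research nurse keeps the envelopes locked and opens each one in order after a patient is recruited. A research assistant with no clinical part in the trial makes the sequence, and on enrolment {16c} states: "Trained investigators will enroll participants".

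**Timing.** Trial status gives first enrolment in August 2019 and planned completion of recruitment before October 2022. The Limitation section names only the short washout.

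**The concern.** Two separate routes to bias are written into the design.

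The first and more important is detection bias. HAMD-24 is an interview scale that needs judgement, and remission is a cut-off on it. A rater who knows the arm and has supported the patient for 12 weeks may score leniently or severely without intending to. If this differs between arms, it enters the remission comparison directly. It also enters the mixed model, which uses the same ratings. Self-rated remission on the QIDS-SR16, a secondary outcome, is no clean check, because participants know their treatment too.

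The second is selection bias. Sealed envelopes stop staff reading the list, but not deducing from past assignments. If a coming arm can be anticipated, it can influence whether or when a patient is entered. Eligibility leaves room for this: the HAMD-24 threshold of 20, the need for an antidepressant and the suicide-risk exclusion all involve judgement.

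**Working it through.** **Plan's own figure.** The article gives no figure on predictability or rating bias. Its sample size reproduces: 2 × (1.960 + 0.842)² / 0.5² = 62.8, so 63 per group, and 63 / 0.70 = 90. An exact t-test gives 64. Nothing below depends on this.

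**1. Who rates the primary outcome.** Four statements, side by side:
- {12}: remission is examiner-rated on the HAMD-24 at week 12.
- {18a}: the HAMD-24 is one of the study's clinical assessments.
- {11c}: assessments at baseline and follow-up are done by the participant's fixed investigator, who also encourages and reminds.
- {17a}: no one is blinded.

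Together they leave the primary outcome with an unblinded rater who is involved in the patient's adherence. This is stated, not inferred from silence.

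**2. What a small rating shift could do (illustration only).** The article gives no expected week-12 HAMD mean or SD. Assume normal scores with mean 12 and SD 7, and a cut at 7.5 for a total of 7 or less.
- No leniency: Φ((7.5 − 12)/7) = Φ(−0.643) = 26.0%.
- 1 point of leniency in one arm: Φ((7.5 − 11)/7) = 30.9%.
- 2 points: Φ((7.5 − 10)/7) = 36.0%.

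Repeating this for means of 10, 12 and 14 and SDs of 6, 7 and 8, one point raises remission by 3.8 to 6.3 percentage points and two points by 7.9 to 12.8. With SD 7, the design effect d = 0.5 is 3.5 HAMD points, so 1 to 2 points is 29% to 57% of it (1/3.5 and 2/3.5). The leniency itself is assumed.

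**3. Predictability of fixed blocks.** Inputs: four arms at 1:1:1:1 ({16a}), five centres ({9}) and 480 patients ({15}), so 480/5 = 96 per centre on average. Assumption: the observer knows the block length b, a multiple of 4, and sees all earlier allocations at the centre.
- An allocation is certain when only one arm has places left in the block. The expected share is 1/(1 + 3b/4).
- The guess rate comes from always naming the arm with most places left. For b = 4 it is (1/4 + 1/3 + 1/2 + 1)/4 = 52.1%. Longer blocks were done by exact recursion over the places remaining.

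| Block length (assumed) | Certain | Of 480 | Guessed correctly (chance 25%) |
|---|---|---|---|
| 4 | 25.0% | 120 | 52.1% |
| 8 | 14.3% | about 69 | 47.0% |
| 12 | 10.0% | 48 | 44.1% |
| 16 | 7.7% | about 37 | 42.1% |
| 20 | 6.3% | 30 | 40.6% |

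**4. Effect of varying the lengths.** This was simulated with 96 patients per centre and an observer who knows the set of lengths but not their order.
- 4/8/12: about 3.5% certain, 46% guessed.
- 8/12: about 4.4% certain, 45% guessed.
- 4/8: about 7.3% certain, 48% guessed.

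Varying the lengths removes most certain allocations but lowers the guess rate only modestly. It does nothing about the unblinded rating.

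**The case against.** A reader might infer that enrolling investigators can work out the coming sequence. The article does not support that. It does not say that sites know the block length, or that each investigator sees colleagues' allocations. A nurse opens each envelope only after recruitment, and a non-clinical assistant makes the list. Deduction needs both the length and the earlier assignments, and even then yields only some allocations. Nor does the article say that the person who enrols a patient is the one who rates them. The allocation point is therefore conditional and secondary.

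A reader might also take the 26% to 31–36% illustration as an estimate of bias. It is not one: mean, SD and leniency are all assumed. Every arm receives pharmacotherapy, so the favoured direction is not evident.

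It would be too strong to say that analysis can do nothing. The model adjusts for gender, age, education and baseline severity, which partly covers selection on those factors. It does not cover unmeasured selection or biased ratings.

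On timing, the lists were already made, and recruitment was planned to end before October 2022. On that schedule new lists may no longer be needed, and week-12 visits may also be over. This limits the remedy, not the point.

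Finally, open-label treatment may be a reasonable choice against treatment as usual. That stands, but it does not require the primary rating to be made by someone who knows the arm.

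**Conclusion.** The main point holds on the article's own statements: an examiner-rated primary outcome is scored without blinding by the participant's own supporting investigator. Rating bias can act directly on the primary result, with unknown size and direction.

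The secondary point holds conditionally. If the fixed length is known or inferred and earlier allocations are seen, 25%, 14% or 10% of assignments are certain for lengths 4, 8 or 12, and the guess rate exceeds the 25% expected by chance at every length examined up to 20. The documents do not show that any of this has happened, or that whole sequences can be foreseen.

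**What to change.** **Rating.** Keep the fixed investigator for contact, encouragement and reminders. Have the week-12 face-to-face HAMD-24 scored by another already trained investigator at the same site who is not told the arm. Where feasible, do the same for the earlier HAMD-24 ratings that feed the mixed model. Because {19} describes an eCRF synchronised in real time across sites, restrict this rater's access so that allocation is not visible. A remote rating from another site would conflict with the face-to-face week-12 visit in {18a}.

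The cost is scheduling, eCRF access control and a line in the operation manual. The article does not say how many raters each site has, so feasibility must be checked locally. The drawback is a change of rater within participant: if only week 12 is masked, it coincides with the primary time point and affects change from baseline.

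**Allocation.** For any lists still to be used, vary block lengths at random (for example 4, 8 and 12) and keep them from the sites. This needs new lists and envelopes and allows slightly larger arm imbalance within a site.

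**If too late.** Where enrolment or week-12 visits are complete, report the fixed blocks and the unblinded rater as limitations, alongside the short washout already named.

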#### Concealment mechanism {16b}

The randomization codes are packed into sealed envelopes in sequence. The envelopes are locked in a cabinet by a research nurse per center, and each envelope will be opened in ascending order to assign intervention after a patient with AFD is recruited.

#### Implementation {16c}

The research assistant without clinical participation in the trial will generate the allocation sequence. Trained investigators will enroll participants. The research nurse at each center will keep and open the envelopes containing randomization codes.

### Assignment of interventions: blinding

#### Who will be blinded {17a}

The iDoT-AFD is an open-label study without blinding.

#### Procedure for unblinding if needed {17b}

The iDoT-AFD is an open-label study without blinding so unblinding will not occur.

### Data collection and management

#### Plans for assessment and collection of outcomes {18a}

M.I.N.I International Neuropsychiatric Interview (MINI) [19] is used to conduct a comprehensive screening. HAMD-24 and Quick Inventory of Depressive Symptomatology (self-report) with 16 items (QIDS-SR16) [20] are applied to evaluate depressive symptoms, Hamilton’s Anxiety Scale (HAMA) [21] is used to assess anxious symptoms, HCL-32 is performed to recognize mania or hypomania symptoms, and Quality of Life Scale with 6 items (QOL-6) [22] is used to evaluate the life quality briefly. Additionally, family history, physical or mental comorbidity, the medication used before, prescription for this time, number of episodes, first-onset time and age, and duration of illness are also questioned and recorded. Adverse events are recorded in adverse events report (AER) forms when needed during the follow-up period. Cognitive function is assessed using the MATRICS Consensus Cognitive Battery (MCCB) [23]. MCCB consists of 10 subtests that mainly reflect the cognitive function of 7 cognitive domains including speed of processing, attention and vigilance, working memory, verbal learning, visual learning, reasoning and problem-solving, and social cognition.

After the 12-week randomized intervention, patients with AFD will be followed up until switching to BD for a maximum of 4 years. Face-to-face interviews, including clinical and neurocognitive assessments, MRI scans, and blood specimen collection, will be scheduled for 12 weeks, 1 year, and 4 years. The interim interviews of clinical assessments will be performed at 2 weeks, 4 weeks, 8 weeks, 6 months, 2 years, and 3 years through offline or online approaches. Patients with AFD will undergo a semi-structured interview at the follow-up time points to determine whether they have experienced mania or hypomania or have been diagnosed with bipolar disorder by psychiatrists during the interval since the previous follow-up. If a patient has experienced mania or hypomania or has been diagnosed with bipolar disorder by psychiatrists during the interval, multidimensional data will be recollected and follow-up will be terminated.

#### Plans to promote participant retention and complete follow-up {18b}

All participants will be generally informed about the significance of follow-up and the value of their contribution before being involved. The investigator will explain the results of the assessments and examinations at every follow-up time point, which may help the participants know more about their mental health condition.

#### Data management {19}

In the iDoT-AFD study, all data are collected electronically using the electronic case report form (eCRF) and synchronized in real-time among all the clinical sites. In this way, the data manager can conduct quality reviews of the database timely. A standardized operation manual of the iDoT-AFD study will be provided to all the investigators of the study. All investigators will be trained about the assessments and study procedures every 6 months to ensure consistent and reliable data collection. The leading PI will have access to the complete trial data and can decide the access to the database.

#### Confidentiality {27}

Participants’ personal information will be managed to maintain confidentiality. The participants’ identification code rather than their names will be used for recording and classifying the eCRF. Only the research associates and IRB have the access to the original medical records to verify the reliability of the data in the trial.

#### Plans for collection, laboratory evaluation, and storage of biological specimens for genetic or molecular analysis in this trial/future use {33}

##### Assessments of metabolic factors in the kynurenine pathway

Five-milliliter venous blood fasting for more than 4 h is collected from participants using the ethylene diamine tetraacetic acid (EDTA) anticoagulant tube. After placing at normal temperature for 30 min, the blood samples are centrifuged at the rate of 3000 rpm, and the plasma is separated and then stored at − 80 °C. All specimens will be examined and analyzed together after finishing collection using ultra-performance liquid chromatography-tandem mass spectrometry.

##### Neuroimaging assessments

Neuroimaging data are acquired using the 3.0-T scanner at available clinical sites. Imaging data including structural MRI, rest state functional MRI, and diffusion tensor imaging (DTI)/diffusion kurtosis imaging (DKI) are collected. All participants are planned to be scanned at baseline, and patients with AFD will also be scanned at 12 weeks, 1 year, and 4 years.

## Statistical methods

### Statistical methods for primary and secondary outcomes {20a}

To evaluate the effectiveness of the 12-week treatment for patients with AFD, we plan to perform an intention-to-treat analysis to pursue our primary outcome. A mixed-effect model for repeated measures will be applied to analyze the main effects of interventions, time, and the interaction on HAMD total scores to find the optimal treatment for patients with AFD. Covariates like gender, age, education, and the baseline severity of depressive symptoms will be added to the model to correct the potential confounding effects.

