### Outcomes {12}

The following is the primary outcome:Clinical remission (examiner-rating), defined as total scores less than or equal to 7 on the HAMD-24 at the end of the 12th week

The following are the secondary outcomes:Clinical remission (self-rating), defined as total scores less than or equal to 5 on the QIDS-SR16 at the end of the 12th weekEarly improvement, defined as a ≥ 20% decrease from the baseline HAMD-24 at the end of the 2nd weekTreatment response, defined as a ≥ 50% decrease from the baseline HAMD-24 at the end of the 12th weekSeverity and incidence of adverse eventsThe time of treatment discontinuation for any causeWorking or learning time lost to any cause associated with the present study

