### Sample size {14}

The sample size estimation refers to the primary outcome. A clinically relevant medium effect size (*d* = 0.5) is expected to be found in a two-sample *t*-test of at least one of the three interventions compared to TAU when calculating the sample size. Using the power of 1−*β* = 80% and the significance level of *α* = 0.05 (two-sided), 63 participants are needed per group. Considering a drop-out rate of ≤ 30%, 90 participants need to be allocated to each group. Finally, we planned to recruit 120 patients per group for a total of 480 included patients with AFD.

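### The declared primary outcome is week-12 remission (yes/no), but the only efficacy model named is for continuous HAMD total scores, and no between-arm analysis of remission is named

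*Protocol article*

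**What the plan says.** Protocol article, Outcomes {12}, gives one primary outcome: "Clinical remission (examiner-rating), defined as total scores less than or equal to 7 on the HAMD-24 at the end of the 12th week". It is binary and fixed at one time point. The secondary outcomes are self-rated remission, early improvement, response, adverse events, time to treatment discontinuation, and lost working or learning time. The HAMD total score as a continuous measure is not among them.

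Protocol article, Statistical methods for primary and secondary outcomes {20a}, opens with "we plan to perform an intention-to-treat analysis to pursue our primary outcome". The next sentence names the model: "A mixed-effect model for repeated measures will be applied to analyze the main effects of interventions, time, and the interaction on HAMD total scores". Its stated purpose is to identify the best treatment for AFD. Gender, age, education and baseline severity are given as covariates.

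Protocol article, Sample size {14}, says "The sample size estimation refers to the primary outcome" and continues "A clinically relevant medium effect size (*d* = 0.5) is expected to be found", using a two-sample t-test of an intervention against TAU with 80% power and two-sided alpha of 0.05. The result is 63 per group, 90 after allowing for drop-out of up to 30%, and 120 per group finally planned.

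**The concern.** Intention-to-treat fixes who is analysed. It does not say which quantity is compared or by what test. The model that follows estimates differences in mean HAMD score, and such a difference does not give a difference in the proportion of patients at 7 or below. The article therefore states a primary outcome and an efficacy model that do not belong together, and the sample size is built on the model's scale, not the outcome's.

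The stake is the treatment conclusion. A reader cannot tell from the article whether the preferred treatment is the one with more remitters or the one with the lower mean score. The power claimed for the primary outcome is also not power for that outcome.

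**Working it through.** **1. Sections side by side**

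| Section | Variable | Analysis named |
|---|---|---|
| Outcomes {12} | Remission at week 12, yes/no | – |
| Statistical methods {20a} | HAMD total score, repeated | Mixed model: arm, time, interaction |
| Sample size {14} | Called the primary outcome | Two-sample t-test, d = 0.5 |
| Additional analyses {20b} | Biomarkers across first-episode AFD, recurrent AFD, BD and HC; switching to mania/hypomania | ANOVA, Kruskal–Wallis, chi-square; prediction model |
| Missing data {20c} | Not specified | Multiple imputation, sensitivity analyses |

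The chi-square tests in {20b} compare diagnostic groups, not treatment arms, and the binary outcome there is switching. No section names a between-arm comparison of remission.

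**2. The plan's own figure**

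n per group = 2(z₀.₉₇₅ + z₀.₈₀)² / d² = 2(1.960 + 0.842)² / 0.25 = 62.8, so 63. The exact t-test gives 63.8, so 64, with 79.5% power at 63. Drop-out: 63 / 0.70 = 90. The stated figures reproduce, as a comparison of two means. No remission rate enters the calculation.

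**3. Mean score and remission can diverge**

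Assume normal week-12 scores with mean 12 in both arms and SD 5 in one, 8 in the other. The mean difference is 0. Remission, a score of 7 or less with the cut at 7.5, is:
- SD 5: Φ((7.5 − 12)/5) = Φ(−0.90) = 18%
- SD 8: Φ((7.5 − 12)/8) = Φ(−0.56) = 29%

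These values are an illustration; the documents give no means or SDs.

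**4. What d = 0.5 means for remission**

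The documents give no remission rates, so TAU remission p₁ is assumed over 20–50%. If d = 0.5 is a shift in a normal score cut at the remission threshold, p₂ = Φ(Φ⁻¹(p₁) + 0.5).

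n per arm = [1.960·√(2p̄q̄) + 0.842·√(p₁q₁ + p₂q₂)]² / (p₂ − p₁)², with pooled variance, no continuity correction and unadjusted alpha.

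For p₁ = 0.30: p₂ = Φ(−0.524 + 0.5) = 0.490; √(2 × 0.395 × 0.605) = 0.691; √(0.210 + 0.250) = 0.678; n = (1.355 + 0.571)² / 0.190², which rounds up to 103.

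Evaluable per arm after 30% drop-out: 120 × 0.70 = 84.

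| TAU remission | Intervention remission | n per arm for 80% | Power at 84 | Power at 120 |
|---|---|---|---|---|
| 20% | 36.6% | 115 | 67% | 82% |
| 30% | 49.0% | 103 | 72% | 86% |
| 40% | 59.7% | 100 | 73% | 87% |
| 50% | 69.1% | 102 | 72% | 86% |

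The t-test on the score with d = 0.5 has 90% power at 84 and 97% at 120.

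**5. Directly assumed remission gaps, same formula**

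| TAU vs intervention | Power at 84 | Power at 120 |
|---|---|---|
| 20% vs 40% | 81% | 93% |
| 30% vs 50% | 76% | 89% |
| 40% vs 60% | 74% | 88% |
| 30% vs 45% | 52% | 67% |
| 30% vs 40% | 27% | 37% |

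**The case against.** The strongest reply is that the article is a condensation. A full protocol is available on request ({31c}), and the sponsor is responsible for making the analysis plan ({5d}). The first sentence of {20a} commits to analysing the primary outcome, and the mixed model comes in a separate sentence without being called the primary analysis. On that reading the remission test is merely unnamed. This stands in part. A reader might infer that remission will never be tested or reported, and the documents do not support that; they show only that no such test is named here. It does not remove the mismatch, because {20a} is not silent: under the heading for the primary outcome it names a model for another variable, and {14} repeats the step.

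A reader might also infer that the treatment conclusion will rest on an effect averaged over all visits, with a large loss of power. The documents do not say so. The model includes the arm-by-time interaction, so week-12 contrasts are available from it, and {20a} does not say which visits enter. Any power figure for an averaged effect depends on the assumed course of the effect. With visits at weeks 2, 4, 8 and 12, 84 per arm and within-patient correlation 0.7 to 0.5, power is 51–60% if the effect grows linearly from zero to d = 0.5, and 96–98% if it is constant from week 2. Neither figure measures the gap between score and remission. That analysts would choose the better-looking result is likewise not something the article shows; {12} fixes remission as primary.

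Two further points are fair. Reading 0.5 as Cohen's h, an effect size for proportions, would also give 63 per group, but the text says d and t-test. And {8} calls the study exploratory, {7} makes the treatment question the second aim, and the score and remission come from the same scale, so the mixed model is relevant supporting evidence. This softens the consequence but does not make it an analysis of the declared outcome.

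**Conclusion.** The point holds as a mismatch between stated sections: the primary outcome is binary week-12 remission, the only efficacy model named is for a continuous score that is not a listed outcome, and the sample size follows the score. It should be corrected, because the article otherwise leaves open which quantity decides between treatments.

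On the sample size, 63 and 90 are sound for a mean difference but are not a calculation for remission. Under the normal-shift assumption, 100–115 evaluable per arm are needed for 80% power on remission instead of 63. The planned 120 per arm gives that power if nearly all patients contribute full information, and 67–73% if only 84 do. For directly assumed gaps, 120 per arm is adequate at about 20 percentage points (74–81% power at 84, 88–93% at 120) but not at 10–15. All of this rests on assumed remission rates and unadjusted alpha. The mismatch itself rests on no assumption.

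**What to change.** Make outcome and analysis match, in one of two ways.

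(a) Keep remission primary and name its analysis in {20a}. An example is logistic regression of week-12 remission on randomised arm, site (the stratification factor), baseline HAMD-24, age, gender and education, in all randomised patients, with the multiple imputation already planned in {20c}. Report the risk difference of each intervention against TAU with its 95% CI. Keep the mixed model as a secondary analysis, list the score as a secondary outcome, and designate the week-12 arm contrasts as its result.

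(b) Declare the week-12 HAMD-24 score primary, with the week-12 contrast from the mixed model as its analysis, and make remission secondary.

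The exact covariates and model under (a) are a matter of choice; the match between outcome and analysis is not. In either case restate {14}: under (a) with assumed remission rates for TAU and intervention, under (b) by saying that it refers to the score.

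Both are changes of wording and need no new data. The cost of (a) is the lower stated power shown above. The cost of (b) is a change of the declared primary outcome, which has to go through the amendment and registry route in {25} and be justified without sight of outcome data by arm.

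### The HAMD mixed model is read through the intervention main effect and the interaction, neither of which tests each arm's difference from TAU at week 12

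*Protocol article*

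**What the plan says.** Outcomes {12} fixes the primary outcome at one time: remission, defined as "total scores less than or equal to 7 on the HAMD-24 at the end of the 12th week". Section 6b names TAU as the comparator. Sample size {14} says that it refers to the primary outcome and looks for an effect in "at least one of the three interventions compared to TAU", by a two-sample t-test with d = 0.5, giving "0.05 (two-sided), 63 participants are needed per group".

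For the trial period, section 18a adds visits before week 12: "The interim interviews of clinical assessments will be performed at 2 weeks, 4 weeks, 8 weeks".

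Statistical methods {20a} then plans a mixed-effect model for repeated measures to "analyze the main effects of interventions, time, and the interaction on HAMD total scores to find the optimal treatment for patients with AFD". Baseline severity is one of the covariates. The article does not say whether baseline HAMD is also a response row. The analysis text names no contrast with TAU and no week-12 contrast, and it does not say which of the listed effects decides.

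**The concern.** The sized question is pairwise (an arm against TAU) and belongs to week 12. The two treatment effects named in section 20a answer other questions. The intervention main effect asks whether the four arms have equal HAMD means averaged over visits. The interaction asks whether the four curves are parallel. Both are joint tests over four arms, so a rejection does not say which arm differs from TAU.

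The conclusion on the optimal treatment could then turn on the shape of the curves. A benefit that builds up slowly is diluted in the visit average. A benefit that is present at week 2 and stays constant does not show in an interaction over post-baseline visits. An arm with faster early relief but no week-12 advantage can produce a significant result. The problem remains if a continuous HAMD analysis is kept, so it is distinct from the fact that remission is binary.

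**Working it through.** **Inputs from the article.** Two-sided α = 0.05, power 80%, d = 0.5, 63 per group, dropout up to 30%, 120 per group planned (section 14); four arms, 1:1:1:1 (section 8); trial visits at weeks 2, 4, 8 and 12 (section 18a).

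**Assumptions, because the article gives no figures.** d is taken on the HAMD scale in SD units. Variance is equal at all visits. Correlation is compound-symmetric (ρ = 0.3, 0.5, 0.7) or first-order autoregressive (0.7). Data are complete, without covariate adjustment. One arm differs, in a two-arm version (that arm and TAU) and a four-arm version (the other three equal).

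**The plan's figure.** n = 2(1.960 + 0.842)²/0.5² = 62.8, so 63; 63/0.70 = 90. Both are reproduced. Exact t-test power at 63 per group is 79.5%. With 120 enrolled and 30% lost, 84 remain.

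**The nulls.** Let δ_t be an arm's difference from TAU at visit t, and δ̄ its mean over the k visits.
- Week-12 contrast: δ_12 = 0.
- Main effect: δ̄ = 0 for all three arms.
- Interaction: δ_t equal at all visits, for all three arms.

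**Noncentrality, two arms, n = 63, compound symmetry** (for four arms replace n/2 by 3n/4 and multiply the degrees of freedom by 3):
- Week 12: λ = (n/2)δ_12²
- Main effect: λ = (n/2)δ̄² / {[1 + (k−1)ρ]/k}, 1 df
- Interaction: λ = (n/2)Σ(δ_t − δ̄)²/(1−ρ), k−1 df

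**Worked at ρ = 0.5:**
- *Linear growth* (0.083, 0.167, 0.333, 0.500; δ̄ = 0.271). Week 12: λ = 31.5 × 0.25 = 7.88, power about 80%. Main effect: 31.5 × 0.0734/0.625 = 3.70, 48%. Interaction: 31.5 × 0.1024/0.5 = 6.45, 54%. With baseline as a fifth response level, δ̄ = 0.217, and the main effect has λ = 31.5 × 0.0469/0.6 = 2.46, 34%.
- *Constant 0.5.* Main effect: 31.5 × 0.25/0.625 = 12.6, 94%. Interaction: λ = 0, 5%.
- *Early only* (0.5, 0.5, 0.25, 0; δ̄ = 0.3125). Main effect: 31.5 × 0.0977/0.625 = 4.92, about 60%. Interaction: 31.5 × 0.1719/0.5 = 10.83, 78%. Week 12: 5%.

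**Approximate ranges over all assumed correlations and both versions, 63 per arm** (% rejecting; single tests by noncentral F and known-variance simulation, either test by simulation):

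| Trajectory | Baseline a response level? | Main effect | Interaction | Either at 0.05 | Week-12 contrast |
|---|---|---|---|---|---|
| Linear to 0.5 | no | 40–61 | 36–82 | 66–89 | 80 |
| Linear to 0.5 | yes | 26–45 | 40–95 | 61–96 | 80 |
| Constant 0.5 | no | 89–99 | 5 | 90–99 | 80 |
| Constant 0.5 | yes | 72–95 | 64–98 | 97–100 | 80 |
| Early only | no | 51–75 | 62–98 | 84–99 | 5 |
| Early only | yes | 34–57 | 76–100 | 90–100 | 5 |
| No difference | either | 5 | 5 | about 10 | 5 |

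At 84 per arm with linear growth, the week-12 contrast has about 90% power. The main effect has 51–74% (35–57% with a baseline level), and either test has 75–99%.

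The week-12 column is for one contrast. Three unadjusted contrasts have a family-wise error above 5% (at most 3 × 5% = 15%), so the 10% for either test should not be set against 5% as if both were trial-wide rates.

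**The case against.** The strongest reply is that section 20a only lists the terms of a standard model: arm, visit, arm-by-visit. The week-12 difference from TAU is a linear combination of those terms, and a condensed article may leave the contrast to an analysis plan that is not shown. That stands in part. The section does not say that an omnibus test decides. It does, however, link these effects to finding the optimal treatment, so the published reading is fixed badly, not merely left out.

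A reader might infer that the plan forfeits 30 or more points of its power. The article does not support this. A loss of that size needs one test to decide alone, and a particular trajectory and correlation. The effects are listed together. If either may count, the loss under linear growth is at most about 20 points and sometimes turns into a gain. With a constant benefit, the main effect over post-baseline visits has more power than the week-12 contrast.

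A reader might also call the early-only rejections false positives. They are not: the arms truly differ at weeks 2 to 8, early improvement at week 2 is a listed secondary outcome, and the trial calls itself exploratory. What remains is that such a rejection does not show a week-12 benefit.

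Last, a week-12 difference in mean HAMD does not test binary remission. That is correct, and the remedy here does not claim to.

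**Conclusion.** The point holds as a mismatch between the effects named for the decision and the comparison that the article sets and sizes. That the nulls differ, and that neither joint test names the arm, follows from the model and needs no assumption.

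The size is conditional. Under linear onset, reliance on the main effect alone costs roughly 20 to 40 points of power at 63 per arm, and more if baseline is a response level. Reliance on the post-baseline interaction alone leaves 5% power for a constant benefit. Accepting either test limits the loss to about 20 points, but raises the global-null error to about 10% and still identifies no arm. These figures rest on d being on the HAMD scale, on complete data, and on the assumed curves and correlations. The change is worth making before analysis.

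**What to change.** In section 20a keep the same model: arm, visit, arm-by-visit, baseline HAMD-24 as covariate, and post-baseline visits as response. Add that the HAMD treatment comparison is the model-based difference of each intervention arm from TAU at week 12, with its confidence interval. Report the overall main effect and interaction as descriptive, and do not use them to name the optimal treatment.

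The cost is a sentence or two of wording, with no new data. The downside is less power than the time-averaged effect if the benefit is constant over the post-baseline visits: about 80% against 89–99% at 63 per arm under the assumptions above. The change does not replace an analysis of week-12 remission, which has to be settled separately.
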